# 1 Research Summary

## 1.1 Abstract

|                                     |                                                                                                                                                                                                                                                                                                                                                                                                                                                                                                                          |
|-------------------------------------|--------------------------------------------------------------------------------------------------------------------------------------------------------------------------------------------------------------------------------------------------------------------------------------------------------------------------------------------------------------------------------------------------------------------------------------------------------------------------------------------------------------------------|
| Study Name                   | A randomized clinical study of topology-optimized splint in the treatment of distal radius fractures                                                                                                                                                                                                                                                                                                                                                                                                                     |
| Research Introduction        | This is a multicenter, randomized controlled clinical study with plans to enroll patients with distal radius fractures. Eligible participants were randomly assigned 1:1 to the intervention group and the control group to be immobilized with a topology-optimized splint or cast, respectively. Participants' fractured wrist were collected before and during the intervention.                                                                                                                                      |
| Purpose of research          | To assess the clinical efficacy and complication rates of topology-optimized splints in the treatment of distal radius fractures following closed manual reduction.                                                                                                                                                                                                                                                                                                                                                      |
| Research subjects            | Meet the diagnostic criteria for distal radius fracture, aged between 18 and 85 years. It is planned to include 110 participants.                                                                                                                                                                                                                                                                                                                                                                                        |
| Research Unit                | Principal Investigator and Affiliation: [name], Ruijin Hospital, Shanghai Jiaotong University School of Medicine                                                                                                                                                                                                                                                                                                                                                                                              |
| Research interventions       | Intervention group: Topology-optimized splint immobilization for 6 weeks, rehabilitation exercise for 6 weeks, 3 days, 7 days, 2 weeks, 6 weeks and 12 weeks of observation follow-up.
Control group: Cast immobilization for 6 weeks, rehabilitation exercise for 6 weeks, 3 days, 7 days, 2 weeks, 6 weeks and 12 weeks of observation follow-up.
Evaluation metrics: Gartland-Werley (G-W) wrist scores, radiographic parameters, visual analogue scale (VAS) scores, swelling degree grade, complication rates |
| Duration of research         | Start in 12,2021,expected to be completed in 6 2023                                                                                                                                                                                                                                                                                                                                                                                                                                                                      |
| Subjects' participation time | 12weeks                                                                                                                                                                                                                                                                                                                                                                                                                                                                                                                  |

## 1.2 Schematic diagram of the study

[figure not shown]

## 2 Research Background

### 2.1 Research significance

Distal radius fractures are a serious public health problem in the world. As the global population ages, osteoporosis and the risk of falls increases, the incidence of distal radius fractures is increasing year by year. From the perspective of patients' wishes and medical insurance, the elderly are more suitable for conservative treatment. Compared with the elderly, the lightweight and breathable external fixation method is more suitable for them. We use topology optimization technology to design the splint to ensure structural strength and improve comfort. Safety tests were carried out using finite element simulation analysis in the early stage, but clinical studies have not yet been carried out. A randomized controlled trial was conducted to verify the efficacy of topology-optimized splints for distal radius fractures.

### 2.2 Research Background

Distal radius fractures (DRFs) represent one of the most frequent fracture injuries encountered in emergency trauma departments. Accounting for approximately 20% of all emergency fractures and 75% of forearm fractures, their prevalence is undeniable. Predominantly resulting from indirect violent injuries like falls with an outstretched hand, sports or traffic accidents, DRFs have a broader reach, commonly affecting both young individuals and those over 65. While younger patients often suffer from high-energy injuries, the elderly tend to experience DRFs due to low-energy incidents. Notably, as the elderly population in China is projected to surpass 200 million by 2025, osteoporotic fractures, with

DRFs as the second most common among the elderly, are emerging as significant public health concerns.

DRFs treatments are dichotomized into surgical and conservative approaches. Interestingly, 12 or 24-month follow-up studies reveal no pronounced difference in pain or functional improvement between these two treatments, fueling debates over the optimal strategy. British guidelines advocate for closed reduction and cast immobilization as primary treatment modalities. However, the conventional cast's drawbacks, like bulkiness and discomfort, have led to innovations in treatment options. With the rise of 3D printing in orthopedics, bespoke splints boasting superior clinical efficacy, lightweight design, and enhanced ventilation are emerging. Such splints could potentially ease patient pain, diminish joint stiffness risks from prolonged immobilization, and expedite wrist function recovery.

The concept of topology optimization, originally from engineering, is being employed to make orthotic devices more lightweight. By mathematically modeling the optimal structural and material distributions for given conditions, the method maximizes strength while minimizing material use. This approach has proven beneficial. For instance, Liao et al successfully reduced the Boston brace's weight by approximately 12.4% without compromising its corrective efficacy. Similarly, Mian et al and Yan et al showcased the potential of topology-optimized splints in enhancing comfort and reducing weight. However, despite these advances, clinical studies examining topology-optimized splints remain scarce. Recognizing this, we employed topology optimization coupled with 3D printing to craft a novel splint from polyamide (PA12). Preliminary safety evaluations of our topology-optimized splint have been conducted through finite element simulations

### **2.3 Expected results of the study**

The purpose of this project was to verify the efficacy and safety of splinting for distal radius fractures. The splint combines engineering topology optimization technology and 3D printing technology to ensure the strength of the structure, improve comfort, and meet the needs of patients with distal radius fractures. Distal radius fracture splints can be used at different times of fracture, which can save a large number of patients with distal radius fractures from surgery, reduce medical costs, and facilitate community promotion.

### **2.4 Potential risk/benefit assessment**

#### **2.4.1 Known potential risks**

All randomized patients may encounter the risks of anesthesia. These risks include: allergic reactions, nerve damage, drug reaction, slowing or stopping of breathing, failure of the anesthetic or sedation analgesia, cardiac arrest, risks that cannot be predicted, permanent disability or even death.

All randomized patients may encounter the general risks of distal radius fracture. These include infection, pain, bleeding, deformity, nerve injury, tendon injury, decreased range of motion, malunion or nonunion, future arthritis (if fracture involves intra-articular) and the need for further surgery.

All patients may encounter the risk of loss of privacy or confidentiality. All research personnel involved in any way with this project will have completed training in the protection of human research participants.

#### **2.4.2 Known potential benefits**

All participants were provided with a professional treatment plan. Each subject will receive good results at the end of the trial.

#### **2.4.3 Potential risk/benefit assessment**

Significant fracture displacement and serious complications may occur in participants, but are rare clinically. During the trial, the patient should be fully informed of the precautions and the necessary

simple and operable treatment methods. In the study, the investigator will evaluate the safety of the subjects. Therefore, the potential risks of this study are controllable, and the potential benefits outweigh the potential risks

### 4 Purpose of the study

**Main purpose:** To assess the clinical efficacy of topology-optimized splints in the treatment of distal radius fractures following closed manual reduction.

**Secondary purpose:** To evaluate the effects of topology-optimized splints on radiographic parameters, pain, swelling, and complications of distal radius fractures.

### 5 Study Design

#### 5.1 Overall design

The study was a multicenter, randomized, analyst-blind controlled trial. Each subject was randomly assigned to an intervention group or a control group in chronological order of visit. The intervention group was immobilization with topology-optimized splint, and the control group was immobilization with cast. After 6 weeks of immobilization, the patient was instructed to perform wrist rehabilitation exercises and the clinical outcomes were evaluated.

#### 5.2 Study endpoints

Subjects are considered to have completed all studies if they have completed all phases of outcome assessment or follow-up according to the study protocol.

#### 5.3 Sample size

The sample size was calculated by PASS software (NCSS, Kaysville, UT) with sample allocation ratio of 1:1 between 2 groups with reference to other studies ( $n=94$ ). The difference in G-W score effective rate between the intervention group (96%) and the control group (77%) was 19% at 3 months, with a 2-sided 5% of type I error probability, and an 80% of power, allowing drop-out rate of 10%, a total of 110 cases were finally required for enrollment.

### 6 Research Subjects

#### 6.1 Eligibility Criteria

In order to be eligible to participate in this study, an individual must meet all of the following criteria:

1. acute distal radius fracture
2. with men or women aged 18 to 85 years old
3. patients with DRFs were classified as type A and type B fractures according to AO/OTA classification
4. fresh closed fractures that have not been combined with other parts of the fracture and have not received other treatment methods
5. fresh closed fractures that have not been combined with other parts of the fracture and have not received other treatment method
6. participants who were willing to cooperate with the doctor for voluntary follow-up

## **6.2 Exclusion Criteria**

An individual who meets any of the following criteria will be excluded from participation in this study:

1. patients with acute open fracture or pathological fracture
2. patients with bilateral DRFs
3. patients who cannot achieve functional reduction after closed reduction of fracture (radiographic criteria after reduction: dorsal angulation  $>10^{\circ}$ , radial inclination  $<15^{\circ}$ , or radial shortening  $>3$  mm)
4. Patients with rheumatic disease who need to take hormone for a long time; patients with serious cardiovascular and cerebrovascular diseases, diabetes, neurological or psychiatric diseases
5. patients with wrist skin damage, infection and ulceration
6. patients who do not agree to be randomized
7. patients with current substance abuse

## **6.3 Study Subject Recruitment**

Study subjects were recruited by surgeons and clinical coordinators (CRCs). During the eligibility screening of patients with distal radius fractures in the outpatient and emergency department of Shanghai Ruijin Hospital and Shanghai Yangpu District Hospital of Traditional Chinese Medicine. Subjects will be enrolled after signing an informed consent form, being diagnosed by surgeons and CRC, and being evaluated according to the study protocol. Planned recruitment options include, but are not limited to, newspapers, the Internet, and posters.

## **6.4 Methodology of research subject assignment**

Patients were randomly assigned to the topologically optimized splint group or the cast group in 1:1 ratio. Random sequence list generated by SAS (Strategic Application Software, version 9.4; SAS Institute Inc) were sealed in opaque envelopes and distributed to each center. The envelope was opened in front of the patient in chronological order of the patient's visit.

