### **10.2 Analysis of primary and secondary study endpoints**

Analysis of primary study endpoints:

Gartland-Werley (G-W) score: The comparison between the two groups used Student's t-test or the Mann-Whitney U-test for continuous variables, and chi-square test or Fisher's exact test for categorical variables.

Analysis of secondary study endpoints:

Radiographic parameters: mixed linear model to test for differences between groups (participants as random effects, time and group as fixed effects).

visual analogue scale (VAS) score, swelling degree grade: mixed linear model to test for differences between groups (participants as random effects, time and group as fixed effects).

Complication: chi-square test or Fisher's exact test for categorical variables, analyzed by calculating the risk ratios and 95% confidence interval.

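### Two hospitals randomise from their own envelopes, but no planned test or model includes centre: a mildly conservative primary test, some lost precision, and no protection against chance imbalance

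*Protocol*

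**What the plan says.** Section 5.1 calls the trial multicentre. Section 6.3 names the recruiting sites: "outpatient and emergency department of Shanghai Ruijin Hospital and Shanghai Yangpu District Hospital of Traditional Chinese Medicine". Section 6.4 gives 1:1 allocation from a SAS-generated list, with envelopes that "were sealed in opaque envelopes and distributed to each center" and are opened in order of attendance. It does not say whether the list is stratified by centre or blocked.

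Section 10.2 compares the Gartland-Werley (G-W) score between groups by t-test or Mann-Whitney if continuous, and by chi-square or Fisher if categorical. Radiographic parameters, VAS and swelling go into a mixed model with participant as the random effect and "time and group as fixed effects". Complications get a chi-square or Fisher test and a risk ratio with 95% CI. Section 10.1 repeats these choices. Centre appears in none of them, nor in the sample size calculation in 5.3.

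**The concern.** Reduction and application of splint or cast are done by local surgeons, so some difference in outcome between a university hospital and a district hospital is plausible. The protocol gives no size for it.

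Centre is a design factor known for every patient before treatment. Leaving it out has one of two effects, depending on how the list was built:

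- **Balanced within centre:** between-centre variation stays in the error term although the design has removed it from the comparison. Standard errors are too large.
- **Not balanced within centre:** the arms may differ by chance in their mix of hospitals, and the crude estimate carries that difference.

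The protocol names its tests and lists its model terms, so an analysis that follows this text would omit centre.

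**Working it through.** **The plan's own figure.** Inputs from section 5.3: a difference given as "between the intervention group (96%) and the control group (77%) was 19% at 3 months"; alpha is 0.05 two-sided and power is 80%. With the pooled-variance formula and mean rate 0.865:

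n per arm = [1.96 × √(2 × 0.865 × 0.135) + 0.842 × √(0.96 × 0.04 + 0.77 × 0.23)]² / 0.19² = 49.6, so 50 per arm and 100 in total.

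Adding 10% gives 100 × 1.10 = 110, the stated total (100 / 0.90 would give 112). The figure reproduces, and centre plays no part in it.

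**Assumptions.** The documents give no centre-specific rates and no split of patients between hospitals. I take 100 evaluable patients, a 50:50 split unless stated, and centre gaps of 0 to 30 points around the protocol's 77% control rate.

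**Balanced within centre, binary outcome.** The plain test uses variance p(1 − p). The true variance of the comparison is smaller by g²/4, where g is the centre gap. The ratio is 1 − (g²/4) / [p(1 − p)]. With p = 0.77 and g = 0.20, it is 1 − 0.0100 / 0.1771 = 0.944, and the type I error is 2Φ(−1.96 / √0.944) = 4.4%.

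Simulation (20,000 trials per row, common odds ratio across centres, overall rates 77% and 96% for power):

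| Centre gap | Type I, plain | Type I, stratified | Power, plain | Power, stratified |
|---|---|---|---|---|
| 0 points | 5.3% | 5.2% | 85.0% | 84.0% |
| 10 points | 4.7% | 4.8% | 85.5% | 84.7% |
| 20 points | 4.3% | 4.9% | 85.0% | 84.8% |
| 30 points | 3.7% | 5.0% | 86.4% | 87.2% |

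Monte Carlo error on a 5% rate is about √(0.05 × 0.95 / 20,000) = 0.15 points. Across runs and base rates the 20-point figure lies between 4.3% and 4.5%. With success of 95% and 70% (a 25-point gap) the plain test rejects 4.2% under the null. With 95% and 60% it rejects 3.2%. The stratified test stays at about 5%. A 70:30 split gives the same pattern (3.8% for the plain test at 30 points).

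**Balanced within centre, continuous outcome.** With a centre gap of d within-centre SDs, centre explains R² = 0.25d² / (1 + 0.25d²) of the variance:

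- d = 0.2: 0.01 / 1.01 = 1%
- d = 0.5: 0.0625 / 1.0625 = 6%
- d = 0.8: 0.16 / 1.16 = 14%

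That is the share of effective sample size lost. In the mixed models the same variation sits in the between-participant variance.

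**Not balanced within centre.** In simulation the plain test's type I error stays at 5.0% to 5.3%, and the mean null difference is within 0.1 point of zero. In a single trial the shift is (difference in centre mix) × (centre gap):

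- 15-point imbalance, 15-point gap: 0.15 × 0.15 = 2.25 points
- 20-point imbalance, 20-point gap: 0.20 × 0.20 = 4 points

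The SE of the difference in centre mix with 50 per arm is √(2 × 0.25 / 50) = 0.10. A 15-point imbalance is therefore 1.5 SE, with probability about 13%. That is a normal approximation. The exact value moves a few points either way because the mix changes in whole patients.

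**The case against.** A reader might infer that hospital confounds the treatment comparison. The documents do not support that. Patients are randomised 1:1, so centre is unrelated to arm in expectation under either way of building the list. The shifts of about 2 or 4 points belong to one unlucky trial and are not a bias of the method. A reader might also fear extra false positives. Overall there are none: the plain test is at or below its level.

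Other points on that side also stand:

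- The centre gaps are assumptions. Gaps of 25 to 35 points are large beside the 19-point treatment effect, given shared eligibility criteria and surgeons trained in both devices (section 7.2.4).
- On the binary endpoint, stratifying brings almost no power. The plain test is slightly ahead up to a 20-point gap.
- A Cochran-Mantel-Haenszel test covers only the categorical reading of the G-W score, which section 10.2 leaves open.
- At 96% success about 2 failures are expected among 50 splint patients (50 × 0.04), about 1 per centre, so strata can be sparse.

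It can also be said that covariates and list stratification are often left to the SAP, which is not at hand. That carries weight for the list. It carries less for the analysis, because this protocol names the tests and spells out the model terms.

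**Conclusion.** The point holds in a moderate form. The protocol fixes analyses that leave out a design factor known for every patient.

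With balance within centre, the cost is a type I error of about 4.5% or 4.2% instead of 5% at assumed gaps of 20 or 25 points, and 1% to 14% of effective sample size on continuous outcomes. Without it, the test is valid overall, but the crude estimate is exposed to chance imbalance that adjustment would remove. Section 6.4 does not settle which case applies, and a reader should not infer either.

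Nothing here threatens the validity of a positive result or changes the sample size. The case for the change is correct test size, better precision on the continuous endpoints, and no later discretion over whether to adjust. All sizes rest on assumed centre gaps and splits.

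**What to change.** In sections 10.1 and 10.2:

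- Analyse the G-W effective rate with a Cochran-Mantel-Haenszel test stratified by centre, and report a centre-stratified risk difference with 95% CI. Where failures are few, use an exact stratified test in place of Fisher.
- If the G-W score is analysed as continuous, use a linear model with group and centre, or the van Elteren test in place of Mann-Whitney.
- Add centre as a fixed effect to the mixed models for radiographic parameters, VAS and swelling.

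In section 6.4, state whether the list is stratified by centre. Whether to use blocks within centre is a separate decision: with visibly different devices and envelopes opened on site, short blocks can make the next allocation predictable.

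**Cost.** A few lines of text, no new data, and the sample size stays at 110. If the centres do not differ, the stratified test gives up about 1 point of power on the binary endpoint with balanced allocation (85.0% to 84.0%) and about 1.5 points without it (85.2% to 83.7%).

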##### **Data Entry and Modification:**

Data entry and management are the responsibility of the statistical unit's data manager. A dedicated database is established for data entry and management. To ensure data accuracy, two data managers should independently perform double data entry and verification.

For any questions in the CRF, data managers will fill out a Query Resolution Form (DRQ) and send inquiries to the researchers through clinical monitors. Researchers should promptly respond and return the answers. Data managers will make data modifications based on the researchers' responses, confirm, and enter the data. DRQs can be resent if necessary.

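### Section 6.4 lets site-held envelopes be opened by order of visit rather than after logged, confirmed eligibility, so selection around allocation is neither prevented nor detectable

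*Protocol*

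**What the plan says.** Section 5.1 sets the level of blinding: "The study was a multicenter, randomized, analyst-blind controlled trial". Splint and cast are visible to patient and surgeon, so site staff know each assignment once it is made.

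Section 6.4 describes the concealment. A 1:1 list is generated in SAS, and the allocations "were sealed in opaque envelopes and distributed to each center. The envelope was opened in front of the patient in chronological order of the patient's" attendance. It mentions no numbering, custodian or opening log. Section 7.3 names allocation concealment as a measure against bias but adds no procedure, so 6.4 is the only description.

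Section 6.3 gives recruitment to surgeons and clinical coordinators, and the same roles take part in the assessment: "Subjects will be enrolled after signing an informed consent form, being diagnosed by surgeons and CRC, and being evaluated according to the study protocol".

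Three other places bear on the point:

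- Section 6.2, exclusion 3, removes patients in whom closed reduction fails radiographic limits, so it can be decided only after reduction and X-ray (7.1.1).
- The flow chart in 7.6 puts consent, eligibility and randomization in one Day 0 column.
- Section 8.2 replaces patients who consented and were randomized but did not receive the intervention.

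**The concern.** Allocation concealment has to ensure that the decision to enter a patient is final before anyone who can influence it knows the arm. Section 6.4 orders the opening of envelopes by the patient's visit, which is not the same event as completed entry. On a literal reading, an envelope could be opened for a patient whose eligibility is still open. If that patient is then excluded, or not treated and replaced, the exclusion has been made with the arm known.

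If patients expected to do poorly were lost more often from one arm in this way, the groups would differ in prognosis at entry. The primary Gartland-Werley comparison would then mix device effect with patient selection. The tests in 10.2 cannot separate the two, and an intention-to-treat analysis helps only if the patients lost after the arm was revealed are still in it.

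**Working it through.** No stated figure is in dispute, so the check is mainly of the passages against each other. The sample size is reproduced first to show that the fix leaves it alone.

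**The plan's own figure (5.3).** Inputs: 96% and 77% effective, two-sided 5% error, 80% power, 10% drop-out. The mean rate is (0.96 + 0.77)/2 = 0.865. With the pooled-variance formula for two proportions:

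n per arm = [1.96 × √(2 × 0.865 × 0.135) + 0.842 × √(0.96 × 0.04 + 0.77 × 0.23)]² / 0.19² = (0.947 + 0.391)² / 0.0361 ≈ 49.6, so 50 per arm and 100 in all.

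Adding 10% gives 100 × 1.10 = 110; dividing by 0.90 gives 112. The stated 110 is reproduced closely, and nothing in the calculation depends on how allocation is concealed.

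**The path of one patient.**

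1. *Who decides entry?* Surgeons and coordinators recruit and assess (6.3). They are not blinded to earlier assignments (5.1).
2. *Where are the next allocations?* At the recruiting centre (6.4).
3. *What triggers opening?* The order of visit (6.4). Section 6.3 puts enrolment after consent, diagnosis and evaluation, but does not say that the envelope stays sealed until then.
4. *When is eligibility final?* Not before the post-reduction X-ray, because of exclusion 3 (6.2, 7.1.1). Section 7.1.1 has the splint or cast applied after that X-ray, but is silent on when the envelope is opened. The rows of the 7.6 chart run from consent through criteria to randomization, but all fall on Day 0 and no rule makes that order binding.
5. *What happens to a patient who drops out between opening and treatment?* The patient is replaced (8.2). Section 10.1 names the intention-to-treat and per-protocol principles together and does not say whether the replaced patient is still counted.
6. *Would a departure leave a trace?* None is described. Section 11.4 has the monitor check case records, report forms and protocol compliance. Neither it nor 11.5.1 mentions reconciling envelopes with the list.

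Steps 3 to 5 leave an interval in which the arm may be known while the patient can still leave the trial. Step 6 means that use of that interval would not be seen.

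**Scale.** With 110/2 = 55 per arm, one patient's result is 1/55 = 1.8 percentage points of that arm's effective rate. The planned 19-point difference corresponds to 0.19 × 55 ≈ 10 patients. This shows what one selected patient weighs; it says nothing about how many there would be.

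**The case against.** The safeguards in 6.4 are real: a computer-generated list, sealed opaque envelopes, opening before the patient, and a chronological order. Section 6.3 places enrolment after consent and evaluation. Exclusion 3 rests on radiographic cut-offs rather than free opinion. Numbering, custody and a log may sit in a site procedure that is not shown. All of this stands, and it limits the point to what the wording permits.

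Three stronger readings are tempting, and the documents support none of them:

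- **That recruiters can learn the next arm and steer enrolment.** Nothing shows that a sealed code can be read early, that the whole stack is delivered at once, or that recruiters hold it.
- **That the next arm can be guessed from past ones.** This depends on the block rule, which is not stated. With simple 1:1 randomization, past assignments predict nothing. Guessing also depends on the list and not on where it is kept, so it is no argument against envelopes.
- **That the false-positive rate rises by a given amount.** Any such figure needs an assumed share of steered entries and an assumed prognosis mix. The 96% and 77% in 5.3 are assumed arm rates, not prognostic groups.

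What the objection does not meet is the combination of provisions that are stated: opening by visit, an exclusion settled after reduction, and replacement after randomization. Objective cut-offs limit discretion over who is excluded, but do not ensure that the decision comes before the arm is known.

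**Conclusion.** The point holds as a weakness in the stated procedure, not as evidence of bias. With unblinded staff who both recruit and assess eligibility, concealment rests on those staff, and the protocol neither ties opening to final eligibility and registration nor describes a record that would reveal a departure. The size of any bias cannot be derived from the document.

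The conclusion assumes that the procedure is as the protocol describes it. If a separate randomization procedure already fixes the opening point, numbering and log, it is enough for 6.4 to say so. The change is worth making because it costs little and guards against a bias that later analysis cannot remove.

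**What to change.** Amend 6.4 as follows:

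1. The arm is revealed only after consent, the post-reduction X-ray check and all eligibility criteria are complete and the patient has been entered in a log.
2. Envelopes are numbered sequentially and used in that order. Patient ID, date and time are written on the sealed envelope before it is opened.
3. The monitor already provided for in 11.4 and 11.5.1 reconciles used and unused envelopes with the SAS list.
4. Where the statistical unit can support it, the arm is released from a centrally held list after registration instead. Section 11.5.1 assigns data work to that unit ("Data entry and management are the responsibility of the statistical unit's data manager"), but not allocation, so this would be a new task and is optional.

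In 8.2 and 10.1, state that every patient whose arm was revealed stays in the intention-to-treat set, including any who are replaced.

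No change to blocking is proposed. The present rule is unknown, and small or varying blocks make the next arm easier for unblinded sites to predict than a long unblocked list.

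The cost is a short delay at entry and a little more monitoring work. The sample size and the primary test are unchanged.
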